### Methods in analysis to handle protocol non-adherence and any statistical methods to handle missing data {20c}

A sensitivity analysis will be conducted on the per-protocol sample including participants who (1) completed at least 3 full, consecutive intervention sessions, where a “full” session is defined as at least 60 min under pressure; (2) do not have an “early” colectomy, defined as a colectomy on or before day 3; and (3) do not have protocol deviations for unacceptable treatment adjustments through day 3. Results will be used to complement the primary planned analyses based on the intention-to-treat sample.

Given the short time frame and nature of hospitalization, we do not expect any attrition for the primary endpoint. For secondary analyses beyond day 5, we do anticipate larger dropout. In the event of large amounts of missing data (i.e., more than 10%), multiple imputation analyses will be explored. Mechanisms of missing data will be examined, with an assessment of variability in missing rate by participant characteristics. These summarizations will inform potential biases resulting from missing data. If appropriate, multiple imputation methods will be considered in sensitivity analyses. Results will be compared across approaches to assess the effect of missing data, robustness to various model specifications, and validity of specified models.

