Key secondary outcomes include (1) clinical response, a continuous measure of the sum of Mayo rectal bleeding and stool frequency sub-scores summarized as the mean at day 3; (2) C-reactive protein (CRP), a continuous measure summarized as the mean at day 3; and (3) endoscopic response, a continuous measure defined by the Ulcerative Colitis Endoscopic Index of Severity (UCEIS) summarized as the mean at day 5. Additional secondary endpoints include (1) steroid-free, colectomy-free, clinical remission (Full Mayo score ≤ 2, with no sub-score > 1), a binary indicator summarized as the proportion at day 90; (2) endoscopic improvement, a binary indicator defined by a Mayo endoscopic sub-score of 0 or 1 summarized as the proportion at day 90; (3) endoscopic remission, a binary indicator defined by a Mayo endoscopic sub-score of 0 summarized as the proportion at day 90; (4) mucosal healing, a binary indicator defined by a Mayo endoscopic sub-score of 0 or 1 and a Geboes histology score ≤ 2 summarized as the proportion at day 90; (5) clinical remission, a binary indicator defined by a full Mayo score ≤ 2 with no sub-score > 1 summarized as the proportion at day 5; (6) need for colectomy, a binary indicator summarized as the proportion at day 90 and (7) the proportion at 12 months; (8) Re-hospitalization for an ulcerative colitis flare, a binary indicator summarized as the proportion at 12 months; (9) Urgency Numeric Rating Scale (NRS), a continuous measure summarized as the mean at day 3; and (10) any serious infection or serious adverse event, a binary indicator summarized as the proportion at day 5. Of note, continuous outcomes violating normality assumptions may be summarized with medians.

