### Sample size {14}

Sample size estimates were based on the primary aim of detecting a clinically meaningful increase in the frequency of clinical response/remission in the HBOT arm compared to the control arm. Specifically, we estimate that our primary outcome will be achieved in 30% of hyperbaric oxygen treated patients and in 10% of sham hyperbaric air treated patients. Based on combined phase 2 A and 2B trial data, we found 11 of 22 (50%, 95% CI: 28–72%) patients who received the HBOT achieved normalization of rectal bleeding and improvement in stool frequency [28, 29]. Given the small sample sizes of these trials, we have chosen the lower bound of this confidence interval (30%) for the point estimate of the primary outcome in the HBOT arm. Outpatient moderate-severe ulcerative colitis trials have observed a 10% placebo response rate for resolution of rectal bleeding by day 5 of active therapy. Although our population being recruited is sicker and the anticipated placebo/sham response rate would be lower than seen in outpatient trials, we have chosen a conservative estimate of 10% for the primary outcome in sham treated patients. For 80% power, with 1:1 randomization and a 5% two-sided significance level, we estimate we will need 63 patients per arm to detect an absolute difference in clinical remission of 20% (30% in HBOT arm vs. 10% in Sham), based on the standard sample size calculation formula for a two-sample test of proportions.

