## Data collection and management

### Plans for assessment and collection of outcomes {18a}

Demographic information, medical history, ulcerative colitis disease history, and medication use will be collected from the participant and/or medical record. Stool studies to rule out infectious etiologies of presentation will be conducted during screening. A physical examination at baseline and day 90 will assess for any clinical abnormalities and vital signs will be recorded. Daily standard of care blood work will include complete blood count, CRP, erythrocyte sedimentation rate (ESR), and a basic metabolic panel including albumin.

During the 5-day intervention period, data will be collected by the hyperbaric oxygen therapy staff regarding session completion and duration at pressure. Daily intravenous steroids and venous thromboembolism prophylaxis use will be recorded.

An endoscopy with biopsies for histopathology will be conducted at screening, day 5, and day 90. The Mayo endoscopic sub-score and the UCEIS [42] will be ascertained by local treating providers and/or study investigators. Available videos from procedures will be captured for re-review centrally. Stool samples will be collected at screening/baseline, day 5, and day 90. Pre-packaged collection kits with instructions will be provided to sites and utilized to ensure appropriate collection technique for stool.

Clinical assessments will include the Mayo score, Urgency Numeric Rating Scale (NRS), and the simple clinical colitis activity index (SCCAI). The Mayo score is a validated instrument to measure disease activity and is comprised of 4 components: rectal bleeding, stool frequency, physician assessment, and endoscopy appearance [43]. Each component score ranges from 0 to 3, with a total score ranging from 0 to 12 (mild disease activity: 3–5, moderate disease activity: 6–10, severe disease activity: 11–12). The partial Mayo score (excluding the endoscopic measure) will be assessed daily through the active intervention period, with the total score being assessed at screening, day 5, and day 90 to correspond with the timing of endoscopies. The NRS scale is a newly developed, validated, and reliable score designed to assess the severity of bowel urgency [44]. The urgency and nocturnal bowel movement frequency sub-scores of the SCCAI are a validated tool designed to assess colitis exacerbations [45]. The NRS and SCCAI will be collected daily through the active intervention period and at day 90.

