Additional secondary analyses will incorporate similar models for all additional binary outcomes. Participants receiving a colectomy prior to the time point of analysis will be considered as ‘non responders’ (e.g., no clinical remission or no endoscopic improvement). A linear mixed model will be used for the continuous endpoint NRS, incorporating data from daily assessments as described above in key secondary analyses. As in primary and key secondary analyses, models will include adjustment for the stratification factor. All additional secondary analyses will be assessed using a two-sided type I error rate of 0.05.

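### The plan gives no main-analysis rule for day-90 remission when the endoscopy is missing, so participants whose steroid use or clinical sub-scores already rule out remission drop out of the analysis

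*Protocol article*

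**What the plan says.** All references are to the protocol article.

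- **Outcomes {12}** lists, as the first additional secondary endpoint, "steroid-free, colectomy-free, clinical remission (Full Mayo score ≤ 2, with no sub-score > 1), a binary indicator summarized as the proportion at day 90".
- **Plans for assessment and collection of outcomes {18a}** makes endoscopic appearance one of the four Mayo components. The partial score is taken daily during the intervention, "with the total score being assessed at screening, day 5, and day 90 to correspond with the timing of endoscopies".
- **Statistical methods {20a}** gives the additional binary outcomes models similar to the primary logistic regression, each tested at two-sided 0.05. One failure rule is written: "Participants receiving a colectomy prior to the time point of analysis will be considered as" non-responders.
- **Missing data {20c}** expects more loss after day 5 ("For secondary analyses beyond day 5, we do anticipate larger dropout"). Imputation is to be explored above 10% missing, and its place is then given: "If appropriate, multiple imputation methods will be considered in sensitivity analyses".
- **Data available without an endoscopy:** Section {11b} collects patient-reported outcomes, medication use and disease progression at withdrawal. Section {18a} reviews medication changes and hospitalizations through 12 months.

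**The concern.** Remission here is a conjunction, so one failed component settles the outcome. A participant on steroids at day 90, with a clinical sub-score above 1, or with the three clinical sub-scores summing to more than 2, is not in remission whatever an endoscopy would show. The plan applies this logic to colectomy and to nothing else.

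A logistic model omits participants whose outcome is missing unless a rule assigns one. With colectomy as the only such rule and imputation outside the main analysis, known failures without an endoscopy are left out. Participants doing badly may well be the likelier ones to skip a day-90 endoscopy. Reported remission rates would then be too high. If the skipping differs by arm, the comparison that informs the durability objective would be biased too.

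**Working it through.** **The plan's own figure.** Sample size {14} states "For 80% power, with 1:1 randomization and a 5% two-sided significance level", with "30% in HBOT arm vs. 10% in Sham", and arrives at 63 per arm. The pooled formula without continuity correction gives

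n = [1.96·√(2·0.20·0.80) + 0.8416·√(0.30·0.70 + 0.10·0.90)]² / 0.20² = (1.1087 + 0.4610)² / 0.04 = 61.6, so 62.

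Power at 63 is 80.9%. The figure reproduces. It concerns the day-5 primary endpoint and is not touched by this point. The article gives no day-90 rate and no dropout rate, so everything below is illustration.

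**Formula.** Let p be true remission in an arm, and m_r and m_n the shares of remitters and non-remitters without an endoscopy. Then

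- observed rate = p(1−m_r) / [p(1−m_r) + (1−p)(1−m_n)]
- observed odds = true odds × (1−m_r)/(1−m_n)

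The odds ratio is unchanged when (1−m_r)/(1−m_n) is the same in both arms, and biased otherwise.

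**Equal skipping.** Assume p = 40% and 25%, with m_r = 10% and m_n = 30% in both arms.

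- HBOT: 0.36/(0.36 + 0.42) = 46.2%
- Sham: 0.225/(0.225 + 0.525) = 30.0%
- Odds ratio: (0.36/0.42)/(0.225/0.525) = 2.00, equal to the true (0.40/0.60)/(0.25/0.75) = 2.00

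Both rates are too high and the difference moves from 15 to 16 points, but the odds ratio is right.

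**Only known failures missing.** Here m_r = 0, so observed rate = p/(1−d), where d is the share of the arm missing. The relative inflation is 11% at d = 10%, 25% at 20% and 43% at 30%. Type I error comes from 200,000 simulated trials of 63 per arm with an unadjusted two-proportion z test.

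| True HBOT/sham | Missing HBOT/sham | Observed | Odds ratio (true) | Type I error |
|---|---|---|---|---|
| 30/30% | 20/20% | 37.5/37.5% | 1.00 (1.00) | 5.0% |
| 30/30% | 10/25% | 33.3/40.0% | 0.75 (1.00) | 11.0% |
| 30/30% | 25/10% | 40.0/33.3% | 1.33 (1.00) | 10.9% |
| 30/30% | 10/30% | 33.3/42.9% | 0.67 (1.00) | 16.8% |
| 40/25% | 10/25% | 44.4/33.3% | 1.60 (2.00) | – |
| 40/25% | 25/10% | 53.3/27.8% | 2.97 (2.00) | – |

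In the second row, 0.10/0.70 = 14% of HBOT failures and 0.25/0.70 = 36% of sham failures skip. That is a marked difference between arms.

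**With known failures scored as non-remission,** the null rows return to 30% versus 30%, and type I error to between 5.0% and 5.1%.

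**The case against.** The article never says that participants without an endoscopy are excluded, and the colectomy sentence is not stated to be exhaustive. Scoring a composite from partial components is often left to the analysis plan, which is not shown; section {11b} refers to it for handling colectomy. This stands as a caution, since a fuller rule may exist. But the article itself fixes a colectomy-only rule and a conditional, sensitivity-only place for imputation, and an analysis plan that follows it would inherit both.

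Four stronger readings are tempting and are not supported.

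- **That the treatment effect must be biased.** It need not be. With equal skipping among failures the odds ratio is unbiased. Participants and treating providers are masked, and nothing in the documents shows different skipping by arm.
- **That dropouts as a group are already known failures.** Someone who misses the day-90 visit has no scheduled day-90 sub-scores. The rule reaches those who attend without an endoscopy, or whose day-90 steroid use is known. What share that is cannot be told from the documents. An earlier re-hospitalization or rescue drug does not by itself fail the day-90 definition.
- **That this contradicts the intention-to-treat statement in {20a}.** That sentence is about primary analyses and analysis by assigned arm, not missing secondary outcomes.
- **That all endoscopy-based endpoints share the problem equally.** For endoscopic improvement, endoscopic remission and mucosal healing, clinical data cannot establish failure. Day-5 remission has the same definitional gap, but section {18b} expects full retention through the intervention, so little may turn on it.

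Durability also does not rest on this endpoint alone: colectomy and re-hospitalization need no endoscopy.

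**Conclusion.** The point holds in a limited form. Omission of participants without an endoscopy is an inference, but it is what the stated model does in the absence of another rule. Overstated remission rates follow whenever failures are likelier than remitters to lack an endoscopy. Bias in the odds ratio needs the further assumption that this selection differs by arm, and it can then favour either arm. The illustrative figures rest on assumed remission and missingness rates, and on every missing participant being a documented failure, which is the most favourable case for the correction. These are additional secondary endpoints outside the Holm family. The change is worth making because it extends the plan's own colectomy logic at very little cost.

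**What to change.** Amend Statistical methods {20a} and Missing data {20c} as follows.

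1. In the main analysis of full-Mayo remission (chiefly day 90, and day 5 where the endoscopy is missing), score as non-remission anyone with a documented failed component at that time point: colectomy, any clinical sub-score above 1, clinical sub-scores summing to more than 2, or, for day 90 only, current steroid use. Steroid use does not count at day 5, because that endpoint is not defined as steroid-free.
2. For participants still undetermined, and for the three purely endoscopic day-90 endpoints, prespecify one main-analysis method. An example is multiple imputation by arm using steroid use, clinical sub-scores, medication changes and the day-5 endoscopic score. Keep the analysis of observed scores only as the sensitivity analysis.

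The cost is plan wording and some programming, slightly lower stated remission rates, and reliance on an imputation model for the undetermined. No new data collection is needed.

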### Plans to give access to the full protocol, participant-level data, and statistical code {31c}

Participant level data will be transferred to the NIDDK central repository at completion of the study. Statistical code will be available upon request.

## Oversight and monitoring

### Composition of the coordinating centre and trial steering committee {5d}

The HBOT-UC study is governed by committees designed to oversee specific aspects of study conduct. The Executive Committee will include NIDDK representatives, the Clinical Coordinating Center PI, and the Data Coordinating Center PI. The Executive Committee is tasked with setting the overall direction for the study, including reviewing ongoing study progress, establishing the study subcommittees, and appointing subcommittee chairs. The Steering Committee will include approximately 2–4 site PIs, representing the clinical centers, and all members of the Executive Committee. The Steering Committee will be charged with implementing, coordinating, and managing the trial. Subcommittees will be formed to (1) monitor recruitment and retention, (2) track amount and quality of samples transferred to biorepository and NIDDK central repository, (3) review revisions of the Manual of Procedures and training materials, (4) review authorship and dissemination of results in presentation and publications, (5) review all ancillary study proposals, and (6) ensure compliance with NIDDK Data Sharing Policies and National Institutes of Health Public Access Policy. A non-significant risk designation for our trial has been obtained from the FDA. We will follow abbreviated reporting requirements, but an investigational device exemption is not required.

### Composition of the data monitoring committee, its role and reporting structure {21a}

The HBOT-UC study has an independent DSMB appointed by NIDDK to oversee study participant safety. The DSMB will receive reports on study progress and safety as well as data quality. Participants in both arms will be assessed for serious and for non-serious adverse events throughout the study period. The DSMB will meet on a semi-annual basis to monitor cumulative safety data and data quality.

### Adverse event reporting and harms {22}

All adverse events (AEs) (not including expected ulcerative colitis-related events (UCREs)) experienced by the participant between the signing of the ICF and end of study visit will be reported. All events meeting criteria for a Serious Adverse Event (SAE) will be documented in the database. Expected UCREs (e.g., diarrhea, blood in stool, or colectomy) will not be documented as AEs unless the event is of greater intensity, frequency, or duration than expected or the investigator believes there is a reasonable possibility the event was related to the intervention. However, these UCREs will be systematically assessed through various other data collection instruments including the Mayo score. The relationship of the AE to the study intervention and/or other study treatments will be assessed separately by independent medical monitors. Any event meeting the criteria of an unanticipated adverse device effect will be reported to the FDA, sIRB, and NIDDK.

Safety data will be presented by treatment groups, and events will be categorized according to the Common Terminology Criteria for Adverse Events (CTCAE) coding system. Safety analysis will consist of describing AEs, clinical laboratory abnormalities, or changes in vital signs that occur in each treatment group over the follow-up period. Trial publications will include descriptive statistics of all AEs occurring during the study period, which will be provided for each treatment group. Additionally, AEs will be summarized by the number and percentage of subjects experiencing any AEs, any severe AEs, any treatment-related AEs, any SAEs, any treatment-related SAEs, and any AEs leading to study treatment interruption.

### Frequency and plans for auditing trial conduct {23}

Remote monitoring visits will occur approximately once per site per year to perform remote source document verification for one randomly selected participant. NUDACC, in collaboration with the HBOT Steering Committee and NIDDK, may schedule on-site monitoring visits throughout the study as needed. These visits will occur at the discretion of the study team and may be linked to site-specific concerns. These visits may be conducted to follow up on training needs and action items, or if remote source documentation or central monitoring reveals continuing or serious noncompliance with data entry and/or study procedures. Additionally, the sponsor or sIRB may visit the site to conduct an audit of the study in accordance with regulatory guidelines.

### Plans for communicating important protocol amendments to relevant parties (e.g., trial participants, ethical committees) {25}

All protocol modifications will undergo review by the sIRB and will be approved before being released to the sites. Changes will be communicated formally by the DCC and discussed at HBOT Steering Committee meetings, study-wide investigator meetings, and coordination staff committee meetings. Changes will also be communicated to the DSMB and modifications will be made to the ClinicalTrials.gov record.

Any new important information that is discovered during the study and which may influence a participant’s willingness to continue participation will be provided to the participant. Additionally, reconsent will be obtained following any major protocol and ICF modifications, as appropriate.

### Dissemination plans {31a}

Trial results will be disseminated through publication of results in peer-reviewed journals as well as dissemination at national or international conferences.

## Discussion

Demonstrating efficacy of HBOT, to optimize early response to steroids, has the potential to shift the paradigm in management of hospitalized UC flares. Given that HBOT is already widely available nationally and internationally, the intervention would be readily implementable in practice. Strengths of this trial include the pragmatic trial design increasing efficiency and generalizability; the inclusion of geographically diverse centers drawing from a demographically diverse population; and the relevance of key outcomes to patients and clinicians. Operational challenges include the short window in which potential participants must be identified, screened, enrolled, and randomized. The trial requires close communication between the gastroenterology and HBOT teams, to ensure a participant can receive the first HBOT session within 48 h of initiating intravenous steroids. The trial is also relying on a clinical device that is used in routine care for other indications, and accessibility of the chambers or technical support for chamber operations during off-hours may pose a challenge throughout the study period. Other challenges include evolutions in biologic and/or small molecule treatment landscape for moderate-severe UC in the outpatient setting which may pose challenges to recruitment.

## Patient Involvement

Patients were involved in the design of this research through the Participant Centered Care Committee. This committee reviewed patient centricity and feasibility for the study design and endpoints.

## Trial status

The first participant was enrolled in March 2024, and we anticipate enrollment completion by March 2027. At the time of publication, the trial is utilizing protocol version 4.0; November 22, 2024.

## Data Availability

Participant level data and biospecimens will be transferred to the NIDDK central repository at completion of the study. All future researchers who utilize these data and samples must do so under a Usage Agreement.

## Abbreviations

AE: Adverse event
ATA: Atmospheres absolute
CRP: C-reactive protein
DCC: Data Coordinating Center
DSMB: Data and Safety Monitoring Board
ESR: Erythrocyte sedimentation rate
FDA: Food and Drug Administration
HBOT: Hyperbaric oxygen therapy
IBD: Inflammatory bowel diseases
ICF: Informed consent form
IOIBD: International Organization for Inflammatory Bowel Disease
NIDDK: National Institute of Diabetes and Digestive and Kidney Disorders
NRS: Numeric Rating Scale
NUDACC: Northwestern University Data Analysis and Coordinating Center
SAE: Serious adverse event
sIRB: Single Institutional Review Board
SCCAI: Simple Clinical Colitis Activity Index
UC: Ulcerative colitis
UCEIS: Ulcerative Colitis Endoscopic Index of Severity
UCRE: Ulcerative colitis-related event
